# Effects of reminiscence therapy combined with memory specificity training (RT-MeST) on depressive symptoms in older adults: a randomized controlled trial protocol

**DOI:** 10.1186/s12877-023-03967-2

**Published:** 2023-06-29

**Keywords:** Autobiographical memory, Depression, Older people, Reminiscence, Randomized controlled trial

## Abstract

**Background:**

Geriatric depression has become a serious public health problem, and reduced autobiographical memory and increased overgeneral memory, as the main cognitive markers of depression, are not only associated with current depressive symptoms but also associated with the onset and course of depression, which can lead to a range of harms. Economic and effective psychological interventions are urgently needed. The aim of this study is to confirm the effectiveness of reminiscence therapy combined with memory specificity training in improving autobiographical memory and depressive symptoms in older adults.

**Methods:**

In this multicentre, single-blind, three-arm parallel randomized controlled study, we aim to enrol 78 older adults aged 65 years or older with a score of ≥ 11 on the Geriatric Depression Scale, and participants will be randomly assigned to either a reminiscence therapy group, a reminiscence therapy with memory specificity training group or a usual care group. Assessments will be conducted at baseline (T0) as well as immediately post-intervention (T1) and 1 (T2), 3 (T3) and 6 (T4) months post-intervention. The primary outcome measure is self-reported depressive symptoms, measured using the GDS. Secondary outcome measures include measures of autobiographical memory, rumination, and social engagement.

**Discussion:**

We believe that the intervention will play a positive role in improving autobiographical memory and depressive symptoms in older adults. Poor autobiographical memory is a predictor of depression and a major cognitive marker, and improving autobiographical memory is of great significance in alleviating depressive symptoms in older people. If our program is effective, it will provide a convenient and feasible strategy for further promoting healthy ageing.

**Trial registration:**

ChiCTR2200065446.

## Background

Ageing is a global issue. On the one hand, the number of older people is increasing every year, and in 2019, there will be approximately 700 million older people worldwide; the number of people over 80 years old is expected to triple by 2050 [1]. On the other hand, as the human disease spectrum shifts from acute high-mortality infectious diseases to chronic low-mortality diseases, life expectancy has increased dramatically worldwide; however, healthy life expectancy varies across countries and regions [2, 3]. In China, from 2010 to 2020, the proportion of people over 65 years of age rose from 8.2% (111 million) to 18.7% (191 million) and is expected to reach 26.9% (400 million) by 2050 [4], with an average life expectancy of 76.4 years and a healthy life expectancy of approximately 68.7 years, which means that older people will have approximately 8 years of disease-carrying survival [5]. China will face an immense challenge of population ageing in the coming decades, and the physical and psychological health of older people as a public issue needs more attention.

With increasing age, older people have poor physical health, such as a decline in daily activities, poor physical mobility, and the presence of multiple disease comorbidities; psychological problems are also prominent [6, 7]. Due to the sense of uselessness brought about by the decline in physical functions, the change in social roles, social isolation since COVID-19 and worries about the spread of the virus [8], older adults may develop a series of psychological problems such as depression and loneliness, among which the incidence of depression ranks first among psychological disorders in older adults [9, 10], impairing their health and quality of life and resulting in a mortality rate that is 1.8 times higher than that of nondepressed patients. In addition, depressed older adults use more outpatient resources than nondepressed older adults, including frequent appointments and laboratory and radiological tests [11], which brings great economic costs to society [12]. Depressive symptoms in older adults are significantly associated with loneliness [13] and are an independent risk factor for decline in self-rated health [14]. Therefore, cost-effective psychological interventions are urgently needed to improve depressive symptoms in older adults and to effectively prevent further development of depressive symptoms.

There are a number of psychological treatments available to alleviate the symptoms of depression in older adults, such as cognitive behaviour therapy, music therapy, problem-solving therapy, and web-based self-management interventions. However, depression as a mental illness has been extensively studied by psychiatrists. A review of previous psychiatric studies related to geriatric depression found that older adults often have difficulty recalling autobiographical memories (ATMs) of discrete events that occurred at a specific place and time in their lives and instead retrieve overgeneral memories (OGMs)[15]. Autobiographical memory is the storage of personal life experiences, which is crucial to shaping the self and maintaining mental health [16, 17], and studies have shown [18]that when depressed patients are given a cue word, they retrieve fewer specific memories and more overgeneral memories than nondepressed individuals in the control group. OGM is a phenomenon in which it is difficult for individuals to extract specific autobiographical memories; in contrast, it will produce categorical or extended memories [19], which is a cognitive marker of depression. Such an overgeneralized memory style is a vulnerable factor for depression [20]; it is related not only to the current symptoms but also to the onset and course of depression [21, 22], which can lead to a series of harms such as impaired social problem solving, rumination and worsening symptoms of anxiety and depression [23]. In recent studies, psychiatrists have suggested that the treatment effect can be improved by improving this psychopathology-based cognitive marker of depression.

Reminiscence therapy, as a potential psychological intervention to improve depressive symptoms in older adults, has an important therapeutic aspect of enhancing autobiographical memory and is often used interchangeably in the literature due to its similarity to the term “life review intervention” [24]. It enhances older people’s positive affect [25], cognitive functioning [26], social participation [27], quality of life, and ability to adapt to ageing [28] through the recall, narration, and reflection of past experiences. In addition to previous meta-analyses showing the significant effect of reminiscence-based interventions in improving psychological problems and enhancing well-being in older adults [29–31], there are also empirical studies showing that when researchers guided older adults through interventions for reminiscence at different stages of life, the older adults became more resistant to social stress, increased their ability to think and act for themselves, and finally, experienced completeness in the final stages of life [32–34]. However, in terms of the improvement of autobiographical memory, studies have shown that reminiscence therapy is not effective in improving it [35–37], possibly because reminiscence therapy is an inherent normative process of thinking about the past [38], rather than the practice and improvement of specific event details, which cannot significantly improve the effect of autobiographical memory.

Memory-specific training (MeST), as an intervention for improving autobiographical memory in some patients with mood disorders, has a good effect on patients’ difficulties in recalling personal events through the use of clues to recall words. Although MeST is simple and can be implemented singly, the effect is not good [39, 40]; thus, it can also be implemented together with traditional interventions such as reminiscence therapy as an adjunct therapy [40]. Consequently, there have been many studies combining these two therapies.

Currently, reminiscence therapy combined with memory-specific training is mainly used in the psychological treatment of cancer patients in palliative care, and its effectiveness needs further validation, as randomized controlled trials of Life Review Therapy combined with Memory Specificity Training (LRT- MST) by Gitta Kleijn showed no significant differences between the two groups in terms of anxiety, depression, quality of life and autobiographical memory in cancer patients [41, 42]. However, other studies have shown that reminiscence therapy based on autobiographical memory training can be used in future studies to investigate available, cost-effective, low-intensity treatment options for patients experiencing mood disorders [43, 44]; thus, further investigation of this therapy is warranted.

Based on the national situation that depressed older people are increasing year by year in China, this study aims to implement a randomized controlled trial of reminiscence therapy combined with memory specificity training in a Chinese context to investigate whether this therapy can reduce rumination and improve depressive symptoms in older people and improve their psychological health by improving autobiographical memory. In this study, it is hypothesized that older people who participate in reminiscence therapy combined with memory specificity training will report improved autobiographical memory specificity, less rumination, and significantly lower levels of depressive symptoms at postintervention and follow-up time points than older adults receiving usual care and reminiscence therapy alone; we further hypothesize that these improvements will be maintained for 6 months after the intervention.

## Methods

This study was designed, performed and reported according to the Standard Protocol Items: Recommendations for Interventional Trials (SPIRIT) guidelines [45].

### Study Design

A multicentre, single-blind, three-arm, randomized controlled trial will be conducted to assess the effect of reminiscence therapy combined with memory specificity training on improving autobiographical memory in older adults and further assess the effect on improving depressive symptoms in older adults. Based on the screening criteria, 78 participants will be recruited from three nursing homes in the provincial capital of China, and participants will be randomly divided into three groups in a 1:1:1 ratio. Participants in the first group will receive a 4-week intervention with reminiscence therapy, participants in the second group will receive a 4-week intervention with reminiscence therapy combined with memory specificity training, and participants in the third group will receive 4 weeks of usual care, followed by a 24-week follow-up.

Data will be collected at baseline, immediately postintervention, 1 month, 3 months, and 6 months postintervention. The study design is shown in Fig. 1. After the intervention, the same instructions will be given to a third group to ensure that more older adults benefit.

**Fig. 1 Fig1:**
[figure not shown]
Trial flowchart

### Participants

#### Eligibility and recruitment

Participants will be recruited from all three nursing homes simultaneously.

Once a nursing home has a sample of 26 subjects, they will proceed to the next step. Inclusion criteria are age ≥ 65 years; nursing home residence ≥ 3 months; Geriatric Depression Scale score ≥ 11; Mini-mental State Examination score ≥ 21; and voluntary participation in this study. Exclusion criteria include the acute onset of major illnesses such as cardiac, respiratory, digestive, or neoplastic disease; the development of a psychological illness other than depression; the taking of antidepressants or psychotropic drugs; an imminent discharge from a nursing home involved in the study; and receipt of other psychological treatment within the past 3 months.

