### Outcome measures

See Table 4 for an overview of all measurement instruments and timepoints for older people.

**Table 4 Tab4:** Overview of instruments per assessment

Measures	T0	T1	T2	T3	T4	
Demographics	×					
GDS	×	×	×	×	×	
ATM	×	×	×	×	×	
RRS	×	×	×	×	×	
IPA	×	×	×	×	×	
T0: baseline, T1: immediately postintervention, T2: 1month postintervention, T3: 3 months postintervention, T4: 6 months postintervention.						

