#### Autobiographical memory

Participants’ autobiographical memory will be measured by the Autobiographical Memory Test. The Autobiographical Memory Test was developed by Williams and Broadbent in 1987 [52] and is a test that is currently widely used in clinical research; this assessment utilizes a cue word technique in which subjects review past personal experiences through cue words that contain five positive cue words, five neutral words, and five negative cue words. Participants will be given two neutral practice words to practice before the formal test. They will be asked to verbally recall memories related to cue words within 1 min during the formal administration of the test, and the implementer will record the recollections in the form of a transcript. The scoring will be performed by two researchers who are not involved in the administration of the test. The two scorers will classify the participants’ recollections into four categories: specific memory, generalized memory, vocabulary association or nonrecollection and nonresponse, and the scoring will be based on the number of cue words recalled by the participants. Since Chinese scholars have translated the cue words in this test into Chinese, composed a vocabulary database and rated the valence of the vocabulary, the Chinese version of the ATM will be used in this study [53], which has a high internal consistency and a reliability test Kappa coefficient of 0.81–0.95 [54]. Cue words that will be used in the assessments and training are shown in Table 5.

**Table 5 Tab5:** Cue words

pre-test	post-test	follow-up
Strong	Deep Love	Honest
History	Books	Relaxed
Fear	Sadness	Friendly
Security	Interesting	Guilty
Individual	Oval	Nervous
Failure	Reject	Desperate
Excitement	Lively	Patience
Caution	Bread	Agile
Solitude	Doubt	Culture

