### Statistical analysis

A database will be established using EpiData, and the data will be entered by two persons and analysed statistically using SPSS 26.0 software. The measurement data such as scale scores will be expressed as the mean ± standard deviation (x ± s). Count data such as general demographic data will be described by the frequency and percentage. The status of each scale score before and after the intervention within each group and the measurement data between multiple groups will be analysed by repeated-measures ANOVA and simple effects analysis if they are normal and have equal variance, and the statistics will be described by median and mean difference (MD). For measures with skewed distribution, median and quartiles will be used to describe the statistics, and Kruskal‒Wallis multiple comparisons will be used to compare the data between and within groups. Intention-to-treat will be used to process the data and P < 0.05 will be considered statistically significant.

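### Between-arm comparisons of autobiographical memory at single visits use neither the baseline memory score nor the screening MMSE; a baseline-adjusted model would be a modest improvement

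*Protocol article*

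**What the plan says.** All places are in the protocol article.

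- **Eligibility and recruitment.** One inclusion criterion is "Mini-mental State Examination score ≥ 21". An MMSE must therefore be done for every resident who enters.
- **Autobiographical memory.** The test is timed and verbal: "They will be asked to verbally recall memories related to cue words within 1 min during the formal administration of the test". The abstract lists it as one of three unranked secondary outcomes: "Secondary outcome measures include measures of autobiographical memory, rumination, and social engagement".
- **Outcome measures, Table 4.** The memory test is given at T0 and at all four later visits. The table has no MMSE row.
- **Statistical analysis.** Scale scores "will be analysed by repeated-measures ANOVA and simple effects analysis if they are normal and have equal variance". For skewed measures, "Kruskal‒Wallis multiple comparisons will be used to compare the data between and within groups". No covariate is named in either branch.
- **Unit of allocation.** Study Design has participants divided at random 1:1:1. Randomization and blinding uses envelopes to settle which home delivers which intervention.

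**The concern.** MMSE is a natural prognostic factor for a one-minute verbal recall task. It is measured before treatment and is already available, but the named analyses make no use of it. A simple-effects or Kruskal-Wallis comparison of arms at one visit also ignores the T0 memory score. Differences in cognition between residents then enter that comparison as noise. If each home forms one arm, nothing at resident level balances cognition across arms, so a difference between homes enters as bias too.

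Memory is a secondary outcome, but the Background section gives it as the route by which the therapy should relieve depression. The between-arm memory contrasts will therefore be read closely, with only about 24 residents per arm. The skewed branch is a realistic prospect, because the score is a count over a short list of cue words, and Kruskal-Wallis cannot take a covariate.

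**Working it through.** The plan states no figure for this point, so there is none to reproduce. From Sample size calculation I take only 24 per group and the effect size of 0.8, read as a standardised mean difference. The article does not state the metric or tie 0.8 to memory.

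**Assumed inputs (not in the documents).** r = correlation of MMSE with the memory score, the same at T0 and later, 0.2 to 0.5. p = correlation of T0 with later memory, 0.5 to 0.7. D = difference in mean MMSE between two homes, 0.5 SD. Memory has SD 1 at each visit, and the homes differ in T0 memory only through MMSE.

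**1. Single visit, no baseline used.** Adjusting for MMSE alone leaves variance 1 − r², so the effect size becomes 0.8/√(1 − r²). Two-sided t-test, alpha 0.05, 24 per arm:

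| r | Effect size | Power |
|---|---|---|
| 0 (no adjustment) | 0.800 | 0.774 |
| 0.2 | 0.816 | 0.791 |
| 0.3 | 0.839 | 0.812 |
| 0.4 | 0.873 | 0.841 |
| 0.5 | 0.924 | 0.880 |

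Bias without adjustment is r × D: 0.2 × 0.5 = 0.10 SD to 0.5 × 0.5 = 0.25 SD. These figures hold only for a comparison that ignores T0.

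**2. Change from T0, as in the group-by-time test.** Bias is D × (correlation of MMSE with later memory − correlation of MMSE with T0 memory). With equal correlations it is 0. With 0.3 at T0 and 0.5 later it is 0.5 × 0.2 = 0.10 SD.

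**3. T0 memory already in the model.** The share of the remaining variance that MMSE removes is r²(1 − p) / [(1 − r²)(1 + p)].

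- p = 0.7, r = 0.2: 0.04 × 0.3 / (0.96 × 1.7) = 0.7%.
- p = 0.5, r = 0.3: 0.09 × 0.5 / (0.91 × 1.5) = 3.3%.
- p = 0.5, r = 0.5: 0.25 × 0.5 / (0.75 × 1.5) = 11.1%.

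The standard error falls by 1 − √(1 − share), which is 0.4% to 5.7% across the range.

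The bias left after T0 adjustment is r × D × (1 − p).

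- p = 0.7, r = 0.2: 0.2 × 0.5 × 0.3 = 0.03 SD.
- p = 0.5, r = 0.5: 0.5 × 0.5 × 0.5 = 0.125 SD.

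With both covariates the coefficients are (p − r²)/(1 − r²) for T0 and r(1 − p)/(1 − r²) for MMSE. The bias becomes rD[1 − (p − r² + 1 − p)/(1 − r²)] = 0, so the MMSE term removes all of that remainder under these assumptions.

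**4. Cost in degrees of freedom.** At one visit with 3 × 24 = 72 residents, the residual degrees of freedom go from 72 − 3 = 69 to 67 with two covariates.

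**The case against.** **Covariates belong in the analysis plan.** That plan is not shown, and no passage promises adjustment for MMSE. Silence alone would not be a finding. But the Statistical analysis section does more than stay silent: it fixes the tests, and one of them cannot be adjusted. The section on social engagement says that this scale is measured to guard against confounding, yet no named analysis adjusts for it or for anything else.

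**The T0 score already does the work.** This stands for the group-by-time test and is why the gain is small. It does not stand for simple effects or Kruskal-Wallis at a single visit, which use no T0 value. That residents with lower MMSE change differently over follow-up is possible, but nothing in the documents supports it.

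**Bias depends on the unit of allocation.** This stands. Under individual randomisation, leaving MMSE out costs precision and leaves chance imbalance, but causes no systematic bias. With one home per arm, MMSE adjusts only for measured cognition.

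**The correlation may be weak.** This also stands. The floor of 21 narrows the MMSE range and probably lowers its correlation with memory.

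**Stronger readings that a reader might infer.** One is that the memory results as a whole are biased by 0.15-0.25 SD, or that power would rise from 77% to 81-88%. Those values (r = 0.3-0.5) apply only to single-visit comparisons that ignore T0. Another is that MMSE scores are thrown away. The article does not say so; it only fails to list MMSE in Table 4. Nor does it rank memory as a key secondary outcome. Extending the covariate to the depression scale because one of its four factors mentions memory loss has no figure behind it.

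**Conclusion.** The point holds as a minor improvement to the analysis of a secondary outcome. Every resident has a pre-treatment measure of cognition, and the single-visit comparisons of a timed memory test use neither it nor the T0 score. Beyond T0 adjustment, MMSE is worth about 1-11% of residual variance. If homes differ by 0.5 SD in mean MMSE, it is also worth 0.03-0.125 SD of bias. All of this rests on assumed correlations, and the low end is plausible given the MMSE floor. The group-by-time test is largely protected already. The conflict between Study Design and Randomization and blinding over the unit of allocation is a separate and larger problem. No covariate can solve it if arm and home coincide.

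**What to change.** In Statistical analysis, state that arms are compared on autobiographical memory at T1-T4 with a baseline-adjusted model (ANCOVA at each visit, or a mixed model over visits). It should include the T0 memory score and the numeric screening MMSE, each with a visit interaction. When scores are skewed, use the same model with robust or bootstrap standard errors in place of the Kruskal-Wallis comparison between arms. Keep the numeric MMSE in the dataset, and add a T0 row for it to Table 4.

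The cost is a change of wording, one data field for a test already given, and about one degree of freedom per covariate per visit. The skewed branch would then report an adjusted mean difference instead of a rank test, and that should be stated.

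Reconcile Study Design with Randomization and blinding on the unit of allocation separately. The adjusted model should not be presented as a remedy for one home per arm.

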### Sample size calculation

Based on a priori power analysis (G-power3.1.9.7) using a power of 0.90 and error probability of 0.05, with a reference to a literature effect size of 0.8 [46, 47], a sample size of 24 participants per group will be needed. Assuming a 10% drop out rate, a sample size of 78 participants will be initially targeted.

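### The 24 per group cannot be reproduced from the stated inputs; read as d = 0.8 in a two-sided two-sample t-test, it gives about 77% power, not 90%

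*Protocol article*

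**What the plan says.** The protocol article, Sample size calculation, gives these inputs: "using a power of 0.90 and error probability of 0.05, with a reference to a literature effect size of 0.8". The result is that "a sample size of 24 participants per group will be needed". It continues: "Assuming a 10% drop out rate, a sample size of 78 participants will be initially targeted". The section gives the G*Power version but not the test family, the contrast, whether the test is one- or two-sided, whether 0.8 is Cohen's d or Cohen's f, or any correlation between repeated measurements.

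The end of the Background states the hypothesis to be supported: RT-MeST participants are to have lower depressive symptoms "at postintervention and follow-up time points than older adults receiving usual care and reminiscence therapy alone". That makes two pairwise contrasts.

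Study Design says that "participants will be randomly divided into three groups in a 1:1:1 ratio". Eligibility and recruitment says: "Once a nursing home has a sample of 26 subjects, they will proceed to the next step". So 78 means 26 per group. Statistical analysis plans repeated-measures ANOVA with simple effects, and Table 4 shows five assessments (T0 to T4).

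**The concern.** The paragraph prints both inputs and an output, so a reader should be able to get from one to the other. On the usual readings that cannot be done. This goes beyond detail that a journal article leaves to a fuller document, because the printed figures do not fit together under the standard tests.

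The 90% will be used when the results are interpreted. RT-MeST against reminiscence therapy alone compares two active arms, and a null result there would be read as fairly strong evidence against a benefit of d = 0.8. If the pairwise power is about 77%, a true effect of that size would be missed nearly one time in four rather than one in ten.

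**Working it through.** **Inputs.** Power 0.90, error probability 0.05, effect size 0.8, 24 per group (72 in total), 10% dropout and 78 enrolled, all from Sample size calculation; three equal groups from Study Design. Assumptions tried, because the article does not state them: two-sided and one-sided tests; 0.8 as d or as f; f = d/2 = 0.4 where d is converted; for repeated measures, the number of visits and the correlation.

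**1. Two-sample t-test, d = 0.8 (noncentral t).** Noncentrality δ = d·√(n/2), with 2n − 2 degrees of freedom.
- n = 24: δ = 0.8 × √12 = 2.771, df = 46, two-sided critical value 2.013. Power = **0.774**.
- n = 33: power 0.893. n = 34: δ = 0.8 × √17 = 3.298, power 0.902. So **34 per group** are needed.
- One-sided: power at 24 is 0.861; 27 gives 0.895, so **28 per group** are needed.
- Effect detectable at 90% with 24 per group, two-sided: **d = 0.96**.

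**2. One-way ANOVA, three groups (noncentral F).** Noncentrality λ = N·f².
- f = 0.4, N = 72: λ = 72 × 0.16 = 11.52, power 0.853. N = 84 is needed, or **28 per group**.
- f = 0.8, N = 24: λ = 24 × 0.64 = 15.36, power 0.913. Here 24 is the **total** (8 per group). With 24 per group (N = 72), power exceeds 0.999.

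**3. Repeated-measures ANOVA, between-group factor, three groups, f = 0.4.** λ = f²·N·m / [1 + (m − 1)ρ], for m visits with correlation ρ.

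| Visits m | ρ | Total N for 90% | Per group |
|---|---|---|---|
| 5 | 0.5 | 51 | 17 |
| 5 | 0.7 | 66 | 22 |
| 5 | 0.8 | 72 | 24 |
| 2 | 0.7 | 72 | 24 |

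For m = 5, ρ = 0.8, N = 72: λ = 0.16 × 72 × 5 / 4.2 = 13.71, power 0.911. So 72 suffices at each correlation shown and is exactly the requirement at two of them. This tests a group effect averaged over visits (with m = 5, including baseline). It is not a contrast between RT-MeST and either comparator.

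The group-by-time version at f = 0.4 with three groups needs 3 to 11 per group over 2 or 5 visits and ρ from 0.3 to 0.8, so it does not return 24 either.

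**4. Dropout.** 24 / 0.9 = 26.7, so 27 per group or 3 × 27 = 81 in equal groups. The plan's 78 gives 78 × 0.9 = 70.2 completing, or 23.4 per group. Pairwise two-sided power at d = 0.8 with 23.4 per group is 0.763, against 0.774 with 24: a loss of about 0.01.

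**The case against.** The strongest objection is that 77% is not a property of the trial as described. The article names no test or metric, so any single power figure rests on a choice made by the reader. The planned analysis is repeated-measures ANOVA, and with f = 0.4 and five visits 72 participants reach 90% at correlations of 0.5, 0.7 and 0.8. If 0.8 were Cohen's f, 24 would be a total printed as a per-group number, and 24 per group would be more than enough. A baseline-adjusted analysis with a correlation a little above 0.5 would also come out near 24.

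Much of this stands. A reader might infer that the trial is shown to be underpowered, with 77% as its actual power. The documents do not support that; they show a figure that cannot be reproduced and a shortfall on one well-motivated reading.

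The alternatives do not restore the paragraph, however. The repeated-measures route needs a conversion to f, a number of visits and a correlation, none of them stated, and it powers a visit-averaged omnibus effect instead of the hypothesised contrasts. The f = 0.8 route leaves the per-group statement wrong in the other direction. Baseline adjustment is not the analysis described.

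A reader might also treat the dropout line as a material error. It is not: the shortfall is under one participant per group. The limitations paragraph in the Discussion does concede a small sample, but in terms of generalisability, and it does not qualify the 90%.

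**Conclusion.** The point holds in conditional form. The 24 per group does not follow from power 0.90, error probability 0.05 and effect size 0.8 under a two-sided t-test (34 per group), a one-sided t-test (28), a three-group ANOVA at f = 0.4 (28), or the same at f = 0.8 (24 in total). Read as d = 0.8 in a two-sided pairwise t-test, which matches the Background hypothesis, power is about 77% with 24 per group and about 76% with the 70 or so expected to complete.

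Those percentages assume individually randomised, independent participants, a 5% level for each contrast and no baseline adjustment. They should not be presented as the trial's true power. Randomization and blinding describes an envelope draw deciding which nursing home delivers which intervention, whereas Study Design describes participants being divided 1:1:1. If homes are what is allocated, individual-level power does not apply. How the 24 was obtained cannot be determined from the article.

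**What to change.** Keep 78 enrolled and rewrite the Sample size calculation paragraph:

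- Name the test, the contrast, the sidedness and whether 0.8 is d or f. If a repeated-measures calculation was used, give the number of visits and the correlation, and say that it powers a visit-averaged group effect.
- Give the power that those inputs deliver. For a pairwise two-sided t-test at d = 0.8, that is about 76% with about 70 analysed, assuming individually randomised, independent participants.
- Say that this figure does not hold if whole nursing homes are allocated to arms, as Randomization and blinding describes.
- Minor: state about 23 completing per group after 10% dropout instead of 24.

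The cost is one reworded paragraph and, on the pairwise reading, a less favourable stated power. No extra participants are required.
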